### Objectives

Our primary objective is to compare adherence to ICS between asthma patients attending pharmacies assigned to provide the EmPhAsIS intervention to usual care. Our secondary objective is to evaluate the impact of the EmPhAsIS intervention on asthma control, asthma-related quality of life, asthma-related hospital admissions, and use of reliever medications during the follow-up period. Our third objective is to evaluate the cost-effectiveness of the EmPhAsIS intervention from a societal perspective over a 10-year time horizon.

### Participants

#### Pharmacies

Pharmacies will be recruited from an existing database of community pharmacies we have partnered with, of which pharmacists have indicated interest in collaborating with us. Pharmacies (the clusters) will be randomized in a 1:1 ratio to intervention or usual care. All recruited pharmacies will receive pamphlets that will describe the study protocol and the Global Initiative for Asthma (GINA)’s Pocket Guide for Asthma [36]. All pharmacists will attend an online workshop (webinar) during which they will be trained on the study protocol and provided education on asthma and medication adherence as part of the study. Pharmacists will also attend separate webinars (intervention webinar and usual care webinar) and will receive written study manuals specific to whether they have been assigned to the EmPhAsIS intervention or usual care group. There are no inclusion or exclusion criteria for pharmacies.

#### Patients

Patients eligible for this study are individuals who fill a (incident or prevalent) prescription for ICS (either monotherapy or in a combination inhaler with long-acting beta-agonists) who answer affirmatively to the question ‘Have you ever been diagnosed by a doctor as having asthma?’. In line with the principles of pragmatic trials, our inclusion criteria are not overly restrictive so that the study sample remains representative of the target population. These inclusion criteria are similar to recent pragmatic trials in asthma [37] and are the following: 1) aged 14 years or older; 2) possessing a cellphone with the ability to send and receive text messages; 3) residing in BC, and planning to reside in BC for the next 12 months; 4) having been registered with the medical services plan (MSP, the provincial insurer of medically-required services) in the past 12 months, and planning to remain registered for the next 12 months; 5) not participating in another interventional study; 6) no communication difficulties, such as inability to communicate in English, or significant impairment in vision, hearing, or speech; and 7) consenting to participate in the study. Written informed consent will obtained from eligible patients before enrollment into the study.

We will utilize recruitment strategies used in our prior pharmacy practice studies [38–40], including posters and shelf-talkers. We will also advertise the study through various communication channels available to our research team, including the study website and social media. We will also implement strategies for targeting recruitment, including working closely with participating pharmacies to establish recruitment targets that are appropriate for the community they service. Furthermore, we will also implement regular monitoring of recruitment, including communication (for example, site visits, telephone calls, and/or emails) to discuss challenges and progress as well as offer ongoing support.

### Randomization

Assignment of pharmacies to provide the EmPhAsIS intervention or usual care will be done in a 1:1 ratio with randomly permuted blocks in sizes of four and six. A computer-generated list will be used to ensure balance in the distribution of intervention and usual care groups at any point in the trial while minimizing the risk that research staff may be able to predict group assignment. Clusters will be allocated to intervention or usual care group by one designated research staff member using the computer-generated list. It will not be possible for participating pharmacies to be blinded to which group they are assigned. However, while the trial will be managed by a coordinator who will also be unblinded, team members responsible for data collection (an interviewer who will collect patient-reported data at 0, 6, and 12 months) and analyses (statistical analyst) will be blinded to group allocation.

### Study groups

#### Intervention (EmPhAsIS) group

Patients attending pharmacies assigned to the intervention group will receive the EmPhAsIS intervention which consists of three main pillars: a) patient education, b) SMS-based monthly assessment of adherence to controller therapies, and c) follow-up of non-adherent individuals by community pharmacists.Patient education: the education component will involve the pharmacist discussing patients’ individual treatments, information on the chronic, episodic nature of asthma and the importance of continuous controller therapy, with emphasis on medication adherence.SMS-based monthly assessment of adherence to controller therapies: The principal component of the intervention is monthly text messages, delivered over the 12 month follow-up period, by which patients are asked to provide their level of agreement with the statement ‘I follow my asthma medication plan’. Responses range on a Likert scale (1: Agreeing completely, 2: Agreeing mostly, 3: Agreeing somewhat, 4: Disagreeing somewhat, 5: Disagreeing mostly, and 6: Disagreeing completely). Individuals will be asked to respond by typing back a number (between one and six) corresponding to the response items. This question and the set of responses are the first item in the Adult Asthma Adherence Questionnaire™ (AAAQ) [41]. The AAAQ is a five-item questionnaire developed specifically as a screening diagnostic tool for adherence by care providers, as well as for identifying potential adherence barriers [42]. The first question is a general adherence monitoring question, and questions two to five determine specific barriers to adherence among individuals with low adherence (forgetting, no need, adverse effects, and costs). The AAAQ has been shown to have a high degree of construct validity and has proven to be a strong predictor of adherence, as measured through administrative health data [42]. There are alternative adherence questionnaires [43, 44], but they do not have the predictive power of the AAAQ [44], or consist of too many questions and thus are cumbersome to administer [43]. In addition, the AAAQ is particularly suited to the EmPhAsIS intervention given the separation of the adherence-monitoring question (question one) from those determining specific barriers to adherence (questions two to five). The transmission and receipt of text messages will be centralized and automated using the University of British Columbia (UBC) designed WelTel system. WelTel is an SMS support and engagement platform that will be administered at our research centre and accessed online by pharmacists through the study website. Centralizing text message transmissions minimizes the burden on pharmacists who will not have to send messages themselves, and reduces the delays and potential errors in the evaluation of responses.Follow-up of non-adherent individuals by community pharmacists: If the response to item one of AAAQ, received through SMS, is anything other than one (Agreeing completely), then this would indicate an adherence problem and the individual will be asked the rest of the adherence-barriers questions of the AAAQ (questions two to five) via SMS. Based on the responses, WelTel will generate an AAAQ adherence report that identifies potential adherence barrier(s) (such as cost or fear of side effects) to help facilitate and guide the pharmacist’s follow-up telephone call with the patient. A pharmacist will then follow-up with the individual within the next 24 hours. During the telephone follow-up, the pharmacist will administer the Asthma Control Test (ACT, a five-item validated and widely used questionnaire assessing asthma control) [41]. In separate training provided to pharmacists in the EmPhAsIS intervention group, webinars will provide step-by-step instruction on use of the WelTel platform as well as administration of the ACT over the telephone. Patient responses to the ACT items will be entered into a survey system that will automatically score the questionnaire in order to facilitate this step for the pharmacist. Based on the individual’s response to the ACT, the outcome of this phone interview may be counselling and education to address adherence problems, or a referral to the patient’s physician (if the individual receives a score of 19 or lower in the ACT, which may indicate the presence of uncontrolled asthma). For patients where the adherence problem is unintentional, the pharmacist will provide phone-based counselling and support, for example by clarifying instructions, offering suggestions on incorporating medication taking with the patient’s daily routine, and offering adherence tools such as calendars. For patients where the adherence problem is intentional, the pharmacist can provide education on the risks and benefits of treatment and non-treatment, evaluate adverse effects, and consider medication coverage options (or the use of alternative formulations). Figure 1 illustrates SMS transmission for pillars two and three of the EmPhAsIS intervention along with scenarios for instances of non-responses to the monthly SMS message. Pharmacists will log telephone calls, including response and non-responses, and in instances of non-responses, at least two follow-up attempts will be made.

**Figure 1 Fig1:**
[figure not shown]
**Schematic of transmission of short message service (SMS) assessment of adherence (pillar two) and follow-up of non-adherent patients by community pharmacist (pillar three) of the EmPhAsIS intervention.** AAAQ: Adult Asthma Adherence Questionnaire; ACT: Asthma Control Test.

#### Usual care (control) group

Patients attending pharmacies assigned to the control group will receive usual care. However, it is imperative that the study can distinguish between the impact of the intervention itself and the training that pharmacists and patients receive upon recruitment into the study. Indeed, previous adherence-intervention studies have been criticized because the individuals in the intervention group were more likely to receive an evidence-based education [33]. As such, patients in the control group will receive the patient education component of the EmPhAsIS intervention (pillar one).

### Data collection and study follow-up

The design of the trial and the schematic of data collection and outcomes are illustrated in Figure 2. Pharmacists will screen for eligibility, obtain informed consent, and enroll patients at their pharmacy. Upon patient enrollment, pharmacists will securely fax the individual’s contact information to the study research coordinator. Prospective data will be collected by telephone interview by an interviewer at set time points as follows: 1) sociodemographic characteristics, such as age, education, income, BC provincial health number (baseline); 2) Asthma Control Test and Asthma Quality of Life Questionnaire (AQLQ) (baseline, 6 months, and 12 months); and 3) changes in the enrollment of the individual with the provincial healthcare system, changes in third-party insurance, as well as the frequency of receiving inhaler medications through samples. In addition to prospectively collected outcome data, we will also obtain data for our study sample through BC PharmaNet (http://www.health.gov.bc.ca/pharmacare/pharmanet/netindex.html) [45] and Population Data BC (http://www.popdata.bc.ca) [46] In brief, these are extensive data resources for applied health services research with data holdings spanning information on all dispensed medications, includes drug name (brand and generic), Canadian Drug Identity Code, date dispensed, quantity dispensed, days of supply (BC PharmaNet), outpatient services, hospital separations, and vital statistics (Population Data BC).

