### Outcomes

The primary outcome is adherence to ICS ascertained by the medication possession ratio (MPR), the ratio of the days of medication supplied over the one-year follow-up [47], which will be calculated using BC PharmaNet data. Secondary outcomes include: 1) asthma control at the end of follow-up (measured by the Asthma Control Test [41]; 2) asthma-related quality of life (measured by using the AQLQ [48]); 3) asthma-related hospital admissions; and 4) use of reliever medications during the follow-up period (ascertained from the administrative health data).

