**Schematic illustration of the asthma Markov model.**

## Discussion

In a review of literature published between 1990 and 2002 of adherence interventions in asthma, Bender *et al*. summarized the three key shortcomings of previous adherence intervention studies: reliance on inadequate adherence measures, inclusion of convenience samples of well-motivated patients, and assessments of intervention outcomes artificially boosted by attrition of the least adherent [33]. The design of the EmPhAsIS trial overcomes these key shortcomings of the previous research. First, our objective assessment of adherence, made possible through the unique, data-rich environment of BC, protects us from the biases that arise when adherence is measured subjectively, and from the prohibitive costs and impracticalities of a direct measure of adherence, such as the Medication Event Monitoring System [63]. Second, by applying liberal inclusion criteria and a follow-up plan that does not disrupt individuals’ health behavior, our study is a pragmatic trial with a high degree of external validity. Third, by assessing the primary outcome variable (MPR) in a way that is not affected by voluntary withdrawal from the study, we protect our results from the attrition of the least adherent.

The merit of an mHealth technology is not solely a function of its clinical benefits. Large investments in mHealth may, by diverting resources, result in a shortfall in funding for basic infrastructure, equipment, and staffing elsewhere in the system [64]. Until mHealth interventions are ‘fit for purpose’, healthcare professionals are unlikely to adopt them and this risks implementation failure [64]. By focusing on a familiar and ubiquitous communication technology with low implementation and operation costs, and low burden on the clients (patients and pharmacists), we are confident of the successful uptake of our proposed intervention, provided that its merits are demonstrated.

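### The provincial health number is collected at the post-enrolment telephone interview, so enrolled patients who miss that interview may be unlinkable to PharmaNet and have no primary outcome

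*Protocol article*

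**What the plan says.** The Protocol article, Data collection and study follow-up, sets out this sequence:

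- At the pharmacy: "Pharmacists will screen for eligibility, obtain informed consent, and enroll patients at their pharmacy".
- Next: "Upon patient enrollment, pharmacists will securely fax the individual’s contact information to the study research coordinator".
- Then: "Prospective data will be collected by telephone interview by an interviewer at set time points as follows". The first item on that list is "1) sociodemographic characteristics, such as age, education, income, BC provincial health number (baseline".
- Separately, on administrative data: "we will also obtain data for our study sample through BC PharmaNet", together with Population Data BC. No linkage key or linkage method is named.

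Under Outcomes, the primary outcome is the one-year MPR, "which will be calculated using BC PharmaNet data". Statistical analysis promises an intention-to-treat analysis. The Discussion lists attrition of the least adherent among the key shortcomings of earlier adherence trials, and says this trial avoids it "by assessing the primary outcome variable (MPR) in a way that is not affected by voluntary withdrawal from the study".

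**The concern.** The main strength of an administrative-data outcome is that it can be had for every randomised patient, whether or not the patient goes on cooperating with the study. That strength depends on holding the linkage identifier from the moment of enrolment. As the procedure is written, the identifier is obtained one step later, in a telephone call that the patient may decline or miss.

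Pharmacies are randomised, and patients are described as attending pharmacies already assigned to a group. A loss between enrolment and the baseline call is therefore a loss after allocation. If people who do not answer study calls also refill their inhalers less often, the patients without an MPR would be the ones the Discussion says the design protects against losing. At stake are the completeness of the intention-to-treat population for the primary outcome and, if the arms lose different shares or kinds of patients, the comparison itself.

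**Working it through.** **1. The sequence.** Consent and enrolment take place at the pharmacy. The item described as leaving the pharmacy is the "contact information to the study research coordinator". The provincial health number appears in one place only, the list of baseline interview items. The MPR needs PharmaNet records, and the article gives no other use for the number. For a patient who is enrolled but never interviewed, the procedure as described records no health-system identifier.

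**2. The plan's own figures (Sample size calculation).** The article gives 334 patients before attrition and a target of 370 after about 10% attrition.

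- 334 / 0.90 = 371.1, or 372 rounded up to equal arms. 334 × 1.10 = 367.4, or 368. The stated 370 lies between these and equals 74 × 5, so it is reproduced within rounding.
- No SD is given. With a design effect of 1 + (5 − 1) × 0.06 = 1.24, two-sided 0.05, 80% power and a difference read as 0.10 on the MPR scale, the 334 implies SD = 0.10 × √(334 / (4 × 1.24)) / (1.960 + 0.842) = 0.293.

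**3. Power if some patients have no MPR** (loss shares assumed, SD 0.293 as implied above):

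| Loss | N with MPR | Power, cluster size shrinking | Power, design effect kept at 1.24 |
|---|---|---|---|
| 0% | 370 | 84% | 84% |
| 10% | 333 | 81% | 80% |
| 20% | 296 | 77% | 75% |

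Losses up to about 10% are covered by the existing allowance, so power is not the issue.

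**4. Bias.** Let p be the share unreached in an arm and g the gap in mean MPR, reached minus unreached. The arm's full mean is (reached mean) − p × g, so analysing only reached patients overstates that mean by p × g. The bias in the difference, intervention minus control, is

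p(I) × g(I) − p(C) × g(C),

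which is (p(I) − p(C)) × g when the gap is the same in both arms. The document gives neither p nor g, so all inputs below are assumed:

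| Unreached, intervention v control | g = 0.1 | g = 0.2 | g = 0.3 |
|---|---|---|---|
| 10% v 10% | 0 | 0 | 0 |
| 5% v 10% | −0.005 | −0.010 | −0.015 |
| 5% v 15% | −0.01 | −0.02 | −0.03 |
| 15% v 5% | +0.01 | +0.02 | +0.03 |

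Equal loss with unequal gaps also biases: 10% in each arm, with gaps of 0.1 (intervention) and 0.2 (control), gives 0.10 × 0.1 − 0.10 × 0.2 = −0.01. Against a target of 0.10, the 5% v 15% rows amount to 10% to 30% of the effect sought, in either direction.

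**The case against.** The strongest reply is that the article is a condensed account. It never says that the health number is the linkage key, that it is collected nowhere else, or that the fax carries nothing else. The consent and enrolment forms are not shown, and neither is the data-collection figure. Patients qualify by filling a prescription at the pharmacy, and registration with the provincial insurer is an eligibility criterion, so the pharmacy may well be able to supply an identifier. This stands as far as it goes: the loss of MPR is possible, not established. It does not dispose of the point, because the article is not merely silent. It assigns the number to the telephone interview. If the number is in fact taken at consent, that description is what needs correcting.

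Three stronger readings are tempting, and the document does not support them.

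- **The analysis population shrinks to interview responders.** The article says data will be obtained for the study sample and does not restrict this to those interviewed.
- **The Discussion is flatly contradicted.** Its claim concerns voluntary withdrawal. A patient who withdraws after the baseline interview keeps the MPR, so the claim is too broad only for those lost between enrolment and that interview.
- **Reach must differ by arm because intervention patients receive SMS.** The messages are monthly over follow-up, so there is little or no SMS contact before a baseline call. The Randomization section also says the interviewer is blinded, so calling effort should not differ by arm.

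The reply is also right that the bias figures rest wholly on assumed inputs.

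**Conclusion.** The point holds in a limited form. Under the procedure as written, patients who enrol but decline or are not reached for the baseline interview may be unlinkable and so lack the primary outcome. This rests on one inference, that the provincial health number is the key to PharmaNet. That is the natural reading, since no other health-system identifier is named. The claimed protection from attrition is then secure only from the baseline interview onwards, which fits poorly with an intention-to-treat analysis of all enrolled patients.

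Any resulting bias is of unknown size and sign. The illustrative range is 0.01 to 0.03 on the MPR scale, and there is no bias if losses and gaps are equal across arms. Severity is moderate: the weakness touches the primary outcome and is cheap to remove, but it is not shown to invalidate the trial.

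**What to change.** Record the provincial health number, with written consent to PharmaNet and Population Data BC linkage, on the enrolment or consent form completed at the pharmacy, and fax it with the contact details. Keep the questionnaires and sociodemographic items in the telephone interview. State that MPR will be analysed for every enrolled patient whether or not any interview is completed. If this is already the practice, correct Data collection and study follow-up to say so.

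Baseline asthma control, income and education are adjustment covariates that also come from the interview. Including never-interviewed patients therefore needs a rule for missing covariates. That rule can sit in the analysis plan and is a separate matter from linkage.

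The cost is one form field and a line of consent wording, added to steps that already exist (written consent before enrolment and a secure fax). The small downside is one more identifier on that fax. The Trial status section says recruitment has not begun, so the change can be in place for the first patient. An identifier never collected may be hard to recover later from someone who cannot be reached.

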**Figure 2 Fig2:**
[figure not shown]
**EmPhAsIS trial design and schematic of data collection and outcomes.** ICS: inhaled corticosteroids.

### Outcomes

The primary outcome is adherence to ICS ascertained by the medication possession ratio (MPR), the ratio of the days of medication supplied over the one-year follow-up [47], which will be calculated using BC PharmaNet data. Secondary outcomes include: 1) asthma control at the end of follow-up (measured by the Asthma Control Test [41]; 2) asthma-related quality of life (measured by using the AQLQ [48]); 3) asthma-related hospital admissions; and 4) use of reliever medications during the follow-up period (ascertained from the administrative health data).

### Sample size calculation

Sample size calculations for cluster RCTs must take into account correlation among patients within clusters [49]. We used the formula for calculating sample size, *N*, for cluster RCTs for comparison of means by Donner and Klar [50] inflated by the design effect (inflation factor, 1 + (*m* – 1) *ρ*):
1

where *m* is the average cluster size and *ρ* is the coefficient of the intra-cluster correlation (ICC) or the ratio of between-cluster variance to total variance, σ^2^
[49], μ is the outcome (MPR), and Z indicates the normal Z-score. We drew from published ICC values based on adherence outcomes (0.0143 [51], 0.06 [52]), medication taking outcomes (0.00994 [53], 0.08 [54]), and non-adherence outcomes in cluster RCTs of adherence interventions (0.02 [55], 0.05 [56]). We also drew from our prior cluster RCT in community pharmacies for information on the number of clusters in that study (32 overall, 14 intervention, 18 usual care) [38]. Based on these data, we applied an ICC of 0.06 and calculated the number of patients that will be required to detect a 10% improvement in adherence rate - deemed clinically significant in prior studies [57] and also relevant from a cost-effectiveness perspective based on our previous research [58] - with a power of 80% and a significance level of 0.05, as 334. Accounting for approximately 10% attrition, we determined a target of 370 patients overall. The corresponding number of pharmacies (clusters) is 74 (37 randomized to intervention and 37 to usual care). As such, we target recruitment at five patients per pharmacy.

